## Abstract

Male factor subfertility has increasingly been considered the cause of infertility in couples. Many men with male infertility have sperm problems such as oligozoospermia, asthenozoospermia, or teratozoospermia. Because abnormal semen parameters are idiopathic to some extent, no standard therapy has been established to date. Herbal medicine has been reported to have beneficial properties in the treatment of subfertility, especially in improving semen quality both in vivo and in human studies. Therefore, we intend to investigate the effectiveness and safety of treatment using Korean medicine (KM) for infertile male patients with poor semen quality.

This will be a single-center, prospective, case-only observational pilot study. About 20 male patients with infertility who visit Conmaul Hospital of Korean Medicine will be recruited. We will follow the standard treatment protocol, which has shown good results in the treatment of male infertility. The protocol is composed mainly of a 10-week herbal decoction treatment; acupuncture and/or pharmacopuncture are added when needed. Semen samples, quality of life, and the scrotal temperatures of infertile men will be observed before and after the 10-week treatment with KM.

The study has received ethical approval from the Public Institutional Review Board (approval number: P01-201708-21-008). The findings will be disseminated to appropriate audiences via peer-reviewed publication and conference presentations.

Trial registration: Korean Clinical Trial Registry (CRIS), Republic of Korea: KCT0002611.

## Introduction

1

Male factor subfertility accounts for at least half of all cases of subfertility,^[1]^ including oligozoospermia (low-spermatozoa count), asthenozoospermia (poor sperm motility), and teratozoospermia (abnormal sperm morphology).^[2]^ The cause of the abnormal semen parameters is idiopathic in 30% to 45% of men.^[2]^ Although some causes of male subfertility are treatable, treatment of idiopathic male factor subfertility remains empirical, with little evidence available.^[3]^ Based on limited evidence, antioxidant supplementation in subfertile men may improve live-birth rates for couples attending fertility clinics.^[4]^ Therefore, the use of assisted reproductive technology is usually the option of last resort in these situations. However, whether there are any differences in safety or effectiveness among the different treatments for male subfertility remains uncertain.^[5]^

Herbal medicine has been widely used to treat male infertility and has been shown to significantly improve both the quality and the quantity of sperm both in vivo^[6,7]^ and in human studies.^[8,9]^ Previously, we reported several studies of male idiopathic infertility in which the patients’ semen quality improved or the study participants were successful in fathering a baby spontaneously, despite poor semen quality, using Korean medicine (KM).^[10–12]^

In the present study, the effects of KM on the semen parameters of male infertility patients will be investigated prospectively to verify the clinical effects of KM therapies on male patients with poor semen quality.

## Methods and design

2

### Objective

2.1

To investigate the effectiveness of KM treatment in male infertility, we will evaluate whether KM treatment improves the sperm parameters of men suffering from infertility.

### Design

2.2

The study will be a single-center, prospective, case-only observational pilot study. Fig. 1 shows a flow chart of this study.

**Figure 1 F1:**
[figure not shown]
Flow chart of the study.

### Ethics

2.3

The study has been authorized by the Public Institutional Review Board (approval number: P01-201708-21-008). The protocol accords with the Declaration of Helsinki. Signed informed consent forms will be obtained from all eligible participants before enrollment. This study is registered with the Korean Clinical Trial Registry, Republic of Korea: KCT0002611.

### Participants

2.4

#### Inclusion criteria

2.4.1

(1)Infertile men between 18 and 45 years of age;(2)Men with infertility problems for a period of >1 year with poor semen quality. Poor semen quality will be defined by abnormal semen parameters observed within 2 weeks of visiting our hospital, including oligozoospermia, asthenozoospermia, teratozoospermia, or a combination of these 3 parameters, based on the 2010 World Health Organization (WHO) guidelines^[13]^;(3)Study participants who provide written informed consent;(4)Patients who trust the researchers, are willing to cooperate throughout the study, and comply with the study regulations.

#### Exclusion criteria

2.4.2

(1)Patients with azoospermia;(2)Patients taking antiserotonin, antidepressant, or other psychiatric drugs.

#### Rejection and withdrawal criteria

2.4.3

(1)Voluntary withdrawal from the study;(2)Participants who do not comply with the prescribed 10-week herbal decoction regimen (<80% of the prescribed doses);(3)Patients not available for follow-up.

**Table 1 T1:**
[figure not shown]
Components of Korean herbal medicine.

**Table 2 T2:**
[figure not shown]
Data collection schedule.

### Outcome measures

2.7

#### Primary outcome

2.7.1

The primary outcomes assessed will be the mean difference in total motile sperm count and the values from each sperm test (sperm concentration, motility, and morphology [percentage normal in form]) from baseline to the end of treatment. Semen samples of men with infertility will be evaluated before and after the 10-week treatment with KM. The sperm test will be performed by experienced clinicians from the same hospital to reduce bias in the semen analysis.

#### Secondary outcomes

2.7.2

The secondary outcomes assessed will be changes in the quality of life questionnaire and in digital infrared thermal imaging (DITI).

##### Quality of life

2.7.2.1

The fertility quality of life (FertiQoL) tool is an international instrument that measures quality of life in infertile patients.^[16]^ FertiQoL has been validated in several languages, including Korean. FertiQoL consists of 36 items that assess overall life and physical health (2 items), along with core-related (24 items) and treatment-related (10 items) quality of life. Core subscales consist of emotional, mind–body, relational, and social domains. Treatment subscales comprise environment and treatment tolerability domains. FertiQoL is scored on a 5-point Likert scale (0–4). The sum score is converted to a 100-point scale, and higher scores indicate a better quality of life.

##### DITI

2.7.2.2

Scrotal skin temperature affects sperm output. Scrotal hyperthermia results in impairment of spermatogenesis.^[17,18]^ DITI may provide reliable measurements of testes temperature.^[19]^ We will use DITI to evaluate scrotal skin temperatures from baseline to visit 3 to confirm the effects of KM on scrotal temperature.

### Adverse events (AEs)

2.8

An adverse event (AE) is defined as an undesirable, unintended sign, symptom, or disease that does not necessarily have a cause–effect relationship with the intervention evaluated in the study. We will perform continuous monitoring of AEs and make any relevant decision in this regard on the basis of both objective and subjective signs.

### Sample size

2.9

A pilot study for planning a larger study and estimating its effective size requires an adequate small sample size. The general rule is that at least 10^[20]^ or 12 participants^[21]^ per treatment group is adequate as the required sample size in a pilot study. This study should therefore include at least 12 participants; assuming a dropout rate of 40%, we have calculated the necessary initial sample size to be 20 participants.

### Statistical analyses

2.10

We will analyze the results of treatment through comparisons of paired data because this will be a case-only series. Descriptive statistics will be used for continuous variables, and frequencies for categorical variables. Continuous variables will be analyzed using the paired *t*-test when the assumption of normality is satisfied; otherwise, the Wilcoxon signed-rank test will be used. Categorical variables will be analyzed using McNemar's test. All data will be analyzed using SPSS for Windows software. The level of statistical significance will be set at a 2-sided *P*-value of .05.

## Discussion

3

Recently, a published meta-regression analysis showed a significant decline in sperm counts between 1973 and 2011, driven by a 50% to 60% decline among men from North America, Europe, Australia, and New Zealand who were not selected based on fertility.^[22]^ These findings strongly imply a significant decline in male reproductive health, which has serious implications beyond fertility concerns.^[22]^ A similar decline has been found in young Chinese men, whose semen parameters showed a decreasing trend over a 15-year observational period.^[23]^

Prescription of Korean herbal medicine for the treatment of oligozoospermia, asthenozoospermia, and/or teratozoospermia is common in clinics in Korea. However, only a few clinical case reports have evaluated the effectiveness and safety of KM.^[10–12]^ Therefore, more data are required to provide optimal information to infertile male patients with poor semen quality.

The herbal medicine used in this study has been used for several years to treat male reproductive diseases in Korea, including male infertility and sexual dysfunction. The composition of the medicine is similar to the medicine used in several studies that showed therapeutic effects for male infertility.^[7,8,12]^

Corni Fructus, Schisandrae Fructus, Rubi Fructus, Cuscutae Semen, and Lycii Fructus are herbs that are frequently used in KM to treat male infertility. Each of these 5 herbs exhibits antioxidant properties, and combinations of these herbs have been shown to improve both sperm count and sperm activity.^[6]^ In traditional Chinese medicine, Morindae Radix is widely used to invigorate the kidneys, to support yang (the original energy in the human body) in resisting diseases, and to treat male infertility.^[24]^ An in vitro study showed that oligosaccharides from Morindae Radix acted as a protective agent against oxidative damage to sperm DNA.^[25]^ A mixture of 2 herbal extracts consisting of Epimedii Herba and Angelicae Gigantis Radix increased sperm production by reducing oxidative stress and had a positive effect in a male infertility model.^[26]^ Cynomorii Herba was associated with significant increases in epididymal sperm counts and absolute testes weights in rat testes.^[27]^ These effects might be because of these herbs’ antioxidative properties, which help to restore imbalances caused by excessive levels of reactive oxygen species.

This observational study will allow collection of valuable and reliable data to evaluate the effectiveness of a specific KM protocol for treating male infertility. This study will contribute to the clinical evidence regarding the effectiveness of KM for infertile men with poor semen quality.

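### The study is sized as an uncontrolled planning pilot, but its aim and closing statement claim effectiveness without qualification

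*Protocol article*

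**What the plan says.** **Basis for the size.** Section 2.9 (Sample size) says: "A pilot study for planning a larger study and estimating its effective size requires an adequate small sample size". From rules of thumb of 10 or 12 per group it concludes: "This study should therefore include at least 12 participants". After a 40% dropout allowance it adds: "we have calculated the necessary initial sample size to be 20 participants". It gives no effect size, SD or power.

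**Design.** Section 2.2 describes a single-center, case-only pilot, so there is no comparator. Section 2.4.1 admits men whose semen parameters were abnormal within 2 weeks of the hospital visit. Section 2.7.1 makes the before-after changes in semen values the primary outcomes.

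**Claim.** The Introduction says the effects of Korean medicine (KM) on semen parameters "will be investigated prospectively to verify the clinical effects of KM therapies on male patients with poor semen quality". Section 2.1 (Objective) says "we will evaluate whether KM treatment improves the sperm parameters of men suffering from infertility". Section 2.10 tests paired data: "The level of statistical significance will be set at a 2-sided" P value of .05. The closing paragraph of the Discussion states: "This observational study will allow collection of valuable and reliable data to evaluate the effectiveness of a specific KM protocol for treating male infertility". The article states no limitation arising from the missing control.

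**The concern.** The reason given for the sample size and the claim the study is meant to support do not match. A planning pilot needs an estimate of the change, its spread and the dropout rate. A statement that treatment improves semen quality needs a way to separate treatment from everything else that moves a semen value over 10 weeks. One arm selected on an abnormal value has no such means.

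Either result could be misread. P<.05 could be taken as verified effectiveness although it may reflect regression to the mean or other non-specific change. P>.05 could be taken as no effect although the interval would still be wide. Infertile couples and the planners of the next study might act on either reading.

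**Working it through.** **1. The plan's own figure.** 12 / (1 − 0.40) = 20. This reproduces the number recruited in section 2.9. No power figure is stated, so none can be reproduced.

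**2. Can P<.05 arise without a treatment effect?** The documents give no retest correlation and no position of the cutoff in the source population, so both are assumptions. Assume a standard normal measure, every man below cutoff c on the measure tested, the qualifying sample used as baseline, and correlation ρ between baseline and retest.

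- λ = φ(c)/Φ(c)
- Expected rise with no treatment = (1 − ρ)λ
- Variance of baseline among those selected: v = 1 − cλ − λ²
- SD of the change = √[(1 − ρ)²v + 1 − ρ²]
- Standardised change d = rise / SD of the change. The chance of P<.05 then follows from the noncentral t distribution with n − 1 df and noncentrality d√n. This treats the changes as normal, so it is approximate.

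Example, c = −1 and ρ = 0.5: λ = 0.2420/0.1587 = 1.525; rise = 0.5 × 1.525 = 0.763; v = 1 + 1.525 − 2.326 = 0.199; SD = √(0.25 × 0.199 + 0.75) = 0.894; d = 0.763/0.894 = 0.853.

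| Cutoff | ρ | Rise (population SD) | d | P<.05, n=12 | P<.05, n=20 |
|---|---|---|---|---|---|
| 1 SD below mean | 0.9 | 0.153 | 0.348 | 19.7% | 31.5% |
| 1 SD below mean | 0.5 | 0.763 | 0.853 | 76.7% | 95.1% |
| At the mean | 0.9 | 0.080 | 0.181 | 8.9% | 12.0% |
| At the mean | 0.5 | 0.399 | 0.435 | 28.0% | 45.5% |

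The nominal rate is 5%. Every row rises with n, so recruiting more men does not cure the problem.

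**3. What would a null result say?** The 95% CI half-width for the mean change, in SDs of the change, is t(0.975, n − 1)/√n:

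- n=12: 2.201/3.464 = 0.635
- n=20: 2.093/4.472 = 0.468

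The standardised change detectable with 80% power (paired t-test, two-sided .05) is 0.89 at n=12 and 0.66 at n=20.

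**4. What can the pilot supply for planning?** The 95% limits for the SD, as multiples of the estimate, are √[(n − 1)/χ²]:

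- n=12: √(11/21.920) = 0.708 to √(11/3.816) = 1.698. Squared, a sample size built on the estimated SD could be out by a factor of 0.50 to 2.88.
- n=20: √(19/32.852) = 0.760 to √(19/8.907) = 1.461; squared, 0.58 to 2.13.

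**5. If the before-after change were used as a between-group effect.** Suppose a share s of the change is non-specific and the SD is the same in both calculations. The number needed would then be 1/(1 − s)² times the number planned:

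- s = 10%: 1/0.81 = 1.2
- s = 25%: 1/0.5625 = 1.8
- s = 50%: 1/0.25 = 4
- s = 75%: 1/0.0625 = 16

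**The case against.** The study is openly labelled a pilot in the abstract and in sections 2.2 and 2.9. A declared single-arm pilot is a legitimate design, and asking for a control group would be a preference. The closing paragraph speaks of collecting data and contributing evidence; it sets no decision rule. All of that stands, and it limits the point to how the aim and conclusion are worded. It does not remove the point, because the Introduction speaks of verification, the Objective asks about improvement, and neither is qualified.

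The regression-to-the-mean figures depend on assumptions. They would be smaller if a separate baseline sample is taken after the qualifying one, for a parameter that was normal in some men at entry (section 2.4.1 accepts any one abnormality), and possibly for total motile sperm count, which is not itself an entry criterion.

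Three stronger readings are tempting but not supported:

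- A reader might infer that nothing in the analysis serves the estimation purpose in section 2.9. In fact section 2.7.1 makes the mean difference the primary outcome and section 2.10 adds descriptive statistics, which yield the mean change and its SD. An article may leave interval reporting to a fuller document.
- A reader might infer that a later trial will be undersized, say fourfold. The article does not say that the larger study is controlled, or that the before-after change will be its effect size. Its phrase in section 2.9 could mean effect size or sample size. Undersizing could occur, by a factor that depends wholly on an assumed non-specific share.
- A reader might infer that the article announces an efficacy verdict. It does not.

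**Conclusion.** The point holds as a mismatch between the basis for the size, the single uncontrolled arm and an unqualified effectiveness aim. The sample size arithmetic is right, and the number of men need not change.

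A significant before-after change cannot be attributed to the treatment. Under the assumptions in the working (retest correlation 0.9 to 0.5), P<.05 arises without any treatment effect in about 20% to 77% of studies at n=12 with a cutoff 1 SD below the mean, and in about 9% to 28% with a cutoff at the mean. These are illustrations, not estimates for this population. The interval widths in step 3 need no such inputs beyond approximate normality, and they show that a non-significant result would leave a moderate change open. Confidence is high for the wording mismatch and low for any particular size of the non-specific share.

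**What to change.** - **Introduction, section 2.1 and the closing paragraph of the Discussion:** say that the study estimates the 10-week change in semen parameters and its variability, with retention and adherence, in order to plan a controlled trial. Say that it draws no conclusion that the treatment is effective.
- **Section 2.10:** report the mean change (the median if non-normal) with a 95% CI as the main result, and label P values exploratory.
- **Section 2.9 or the Discussion:** state that the before-after change may include regression to the mean and other non-specific change, and will not by itself be used as the between-group effect of a controlled trial. List what the pilot can supply: the SD, allowing for its uncertainty (0.71 to 1.70 times the estimate at n=12, 0.76 to 1.46 at n=20); the dropout rate; and the baseline-to-follow-up correlation under treatment. That correlation is not test-retest reliability, because the samples are taken before and after treatment.

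Cost: wording, and a more modest claim. No patients, visits or data are added; adherence must already be tracked for the 80% compliance criterion in section 2.4.3.
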